**Figure 1 F1:**
[figure not shown]
Protocol flow.

For this pilot intervention, class size is kept small (5–10 participants) to allow for modifications and explanation of yoga poses that will encourage greater self and body awareness. The yoga therapy approach tailors each pose to the needs and limitations of every individual. Props (chairs, bolsters, blankets, blocks and straps) are used and the postures are modified to accommodate the limitations of the arthritis patients taking the yoga classes.

Participants are encouraged to develop a home practice, which appears to be critical to the effectiveness of the intervention [15]. The last section of each class is dedicated to providing guidance on how to do home practice based on poses taught and information given during each yoga class. All participants receive a yoga mat, blocks, belt, and blanket for their home practice. Participants keep a journal to qualitatively document the frequency of home practice and their experience of participating in the study. Journals are open format, allowing respondents to record their observations/feelings about practicing yoga in their own words [81-84].

This study focuses on the branch of Hatha yoga that uses postures (asanas), breathing techniques (pranayama) and meditation. Within Hatha yoga, there are numerous styles each with a slightly different approach to the physical practice of yoga. This protocol is primarily influenced by the styles of Integral, Iyengar and Kripalu yoga, each of which is considered to focus on proper physical alignment in a gentle and attentive fashion, while also including a strong component of mindfulness during and between physical postures [15,85].

The yoga classes are formatted so that every class builds on the previous class. The contents of class 1 are repeated with additional poses added during each successive class (Table 1).

**Table 1 T1:** Overview of yoga poses

	**Description**	**Yoga poses**

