**Laying foundation:**		
**Classes 1-2**	Warm-up:	Upper body stretches, staff with leg lifts
	Sun Salutations (one side):	Forward fold, mountain (two sides for class 2)
	Standing poses:	Tree, warrior II
	Sitting poses:	Head to knee, spinal twist, yogic seal
	Relaxation:	Sivasana, tense and release, progressive body scan
	Closing:	Side lying, cross-legged
**Class 3**	Discussion of balance poses	Tree, king dancer
**Classes 4-5**	Arm balancing and reclining poses	Inverted plank, (lying) extended leg pose, (lying) spinal twist
**Classes 6-7**	Arm/leg extensions and hip openers	Table and cat/cow-extend arm & opposite leg, downward facing dog-extending one leg, bridge with leg extension, butterfly
**Classes 8-9**	Intro to gentle back bends	Sphinx, locust, bow, camel
**Classes 9-10**	Stamina building	Four sun salutations
**Class 11**		Poses for sciatica
**Class 12**		Pose modifications using the wall
**Class 13**		Restorative poses
**Classes 14-16**		Review, practice, wrap up

This format follows that of the previous randomized research study *Yoga for Arthritis*, conducted through Johns Hopkins University, which explored mediators of yoga practice and health related quality of life measures and disease symptoms in RA and OA patients. Results from the study found benefits of this sixteen-class yoga series created specifically for those with arthritis included:

• A statistically significant improvement in overall physical health, flexibility, and balance.

• A significant reduction in symptoms of depression and improvement in positive affect.

• A significant improvement in pain symptoms and, for those with RA, a significant difference in the number of tender and swollen joints when compared with control subjects receiving the usual medical care [86,87].

[name], a researcher on the Hopkins study and an advanced yoga teacher trained in yoga therapy provided yoga for arthritis training to bilingual yoga instructors recruited to teach for this study. In order to optimize treatment fidelity, all instructors use the same training manual of 16-class sequence used in the Haaz study and all classes are videotaped. Class attendance, the name of yoga instructor, home practice, and reported side effects are recorded during each class session.

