The *functional reach test* is a dynamic measure of stability during a self-initiated movement [118]. Functional reach is the difference (in inches) between a person’s arm length and maximal forward reach with the shoulder flexed to 90 degrees while maintaining a fixed base of support in standing. In a study by Duncan (1990), it was found that functional reach measures were strongly associated with measurements of the center of pressure excursion. The Pearson correlation coefficient was 0.71 and the *R2* using linear regression was 0.51. Analysis of the test-retest reliability of the three primary measures of postural control suggests that functional reach is highly reproducible. The intraclass correlation coefficient (ICC 1, 3) for center of pressure excursion was 0.52, electronic functional reach 0.81, and “yardstick” reach 0.92. [119].

The *timed “Up and Go” test* (TUG) measures, in seconds, the time taken by an individual to stand up from a standard arm chair, walk a distance of 3 meters, turn, walk back to the chair, and sit down [120]. A history of arthritis increases the risk of falling, sensitivity of the TUG for predicting falls was 0.80 and specificity was 0.934 [121,122]. Inter-rater reliability for the TUG is high with a same day, three-rater intra-class correlation coefficient (ICC) of various studies has ranged from 0.99 - 0.992. For validity, moderate to high correlations have been observed with scores on Berg Balance Scale, gait speed, stair climbing, and the Barthel Index of Activities of Daily Living Scale [121].

A *timed floor transfer* is a clinical test of strength, flexibility, function, and problem solving; it measures the time necessary to transfer from standing to the floor and return to standing in any way that participants are able [123]. The time needed is recorded in seconds, then standardized by using body height to determine the speed of this task. Higher values indicate better scores [124]. The interrater reliability for three timed tests (50-ft walk, five-step, and floor transfer) between various pairs of two testers was determined to be excellent (r = .99) [124]. The calculated ICCs were moderately high (ICC_2,1_ = .79, *p* = .0001) on the timed data to determine test–retest reliability in a community-based, predominantly Hispanic population some of whom were diagnosed with arthritis [125].

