This pilot study evaluates the acceptability of offering yoga as an integrative intervention for self-care using the response rate, percent of classes completed, exit interview comments and the percent of patients continuing yoga after three months. Barriers and reasons for continuing/discontinuing yoga are assessed in a brief questionnaire either in person or by telephone, three (3) months after completing yoga classes. Results from the Haaz study were used to determine reasonable measure and time frames for this study. The study found of 102 patients screened, 52% of randomized persons completed the 8-week yoga session [128]. Those who actually started the intervention were very likely to complete it, as attrition was highest prior to the first class [129]. Based on these results, the decision was made to decrease the time from enrollment to start of yoga classes; and to decrease the class size to 5–10 participants per class.

Acceptability of this study will be evaluated based on the response rate, percent of classes completed, exit interview comments and the percent of patients continuing yoga after 3 months. Feasibility will be determined based on exit interview comments and qualitative data. Qualitative field notes will be kept to monitor/document related to issues such as site capability (location/space), personnel (bilingual yoga teachers/investigators), equipment (computers/yoga props), and the amount of modifications needed. A record will be kept of eligible patients who decline and reasons for declining.

Statistical Package for the Social Sciences (SPSS) Version 20.0 will be used to analyze outcome measure data. Descriptive statistics (mean and median) will be used to describe the profiles of the subjects from demographic data gathered. Wilcoxon tests will be used to test differences between baseline and final assessments, for those who complete the study. Pre- and post- changes will be identified; however, no attempt will be made to evaluate statistical significance given the small sample size of the pilot study. An attempt will be made to complete an exit interview for all participants, even those who discontinue participation in the study prior to full completion. Missing data will be managed according to the recommendations of selected measures used in the protocol, or omitted from analyses.

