The feasibility of using a computerized self-interview method (with assistance) will be based on the percent of assistance needed to complete questionnaires, comments collected from the interviewer offering assistance and comments solicited from the participants during the exit interview.

The Medical Advisory Investigator (MAI) will be responsible for the patient safety monitoring. The Principal Investigator will provide a regular report of all protocol activities to the MAI and discuss any concerns. No invasive treatments are provided as part of this protocol. This population will not be exposed to yoga poses (i.e. headstands and shoulder stands) that are most commonly associated with injury. Adverse events and serious adverse events will be monitored at all times during yoga classes and if reported by subjects by telephone. Specific safety instructions will be given as part of every class and pose modifications will be taught to individuals as needed. Participants will be instructed to report side effects immediately should they occur.

Investigators will attend all yoga classes and will ask subjects about side effects during each class session. Subjects will also be instructed to report side effects immediately, to the study PI; by telephone should they occur while practicing at home. Any reported side effects will be documented by the investigators using the weekly flow sheet and reviewed daily by the PI. The PI will report adverse events to the MAI for recommendations and follow-up, and record in the patient record. For research related injury, the subject will be evaluated by NIAMS rheumatology at either the NIAMS CHC or the NIH Clinical Center.

A serious adverse event is defined as any untoward medical occurrences that 1) result in death, 2) are life-threatening, 3) require hospitalization, 4) cause persistent or significant disability/incapacity, 5) result in congenital anomalies or birth defects, 6) are other conditions which in the judgment of the Investigators represent significant hazards. All serious adverse events will be reported to the IRB and to the Clinical Director, within 7 days for death or life threatening adverse event and within 15 days for all others. All adverse events reported under this protocol will be limited to those events which are possibly, probably or definitely related to the research described in this protocol.

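### Active adverse-event questioning is stated only for the 16 classes; the physical tests have no stated capture step, and practice after the classes relies on participants telephoning

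*Protocol article*

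**What the plan says.** All references are to the protocol article.

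- **Monitoring rule** (safety paragraphs, near the end of Methods/design): "Adverse events and serious adverse events will be monitored at all times during yoga classes and if reported by subjects by telephone".
- **Scheduled question** (same paragraphs): "Investigators will attend all yoga classes and will ask subjects about side effects during each class session". The account of the class series, after Table 1, agrees: "Class attendance, the name of yoga instructor, home practice, and reported side effects are recorded during each class session".
- **Home practice**: "Subjects will also be instructed to report side effects immediately, to the study PI; by telephone should they occur while practicing at home". No end date is attached to this instruction.
- **Scope of reporting**: adverse events are reportable if possibly, probably or definitely related to the research. The paragraph on the Natural History protocol then words the principal investigator's monitoring in terms of the yoga intervention and does not mention the tests.
- **Physical tests** (Physical assessment): single leg stance, functional reach, timed up-and-go and a timed floor transfer. For the last, "it measures the time necessary to transfer from standing to the floor and return to standing". NIH rehabilitation staff run the tests at baseline and after the class series. On the up-and-go test the article notes: "A history of arthritis increases the risk of falling".
- **Promotion of home practice** (after Figure 1): "Participants are encouraged to develop a home practice, which appears to be critical to the effectiveness of the intervention".
- **Three-month contact**: "Barriers and reasons for continuing/discontinuing yoga are assessed in a brief questionnaire either in person or by telephone". The proportion still doing yoga at that point is one of the acceptability measures.
- **Exit interview** (Appendix): printed in full. It is completed after the last class, and dropouts are telephoned to try to complete it.

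**The concern.** How an event is looked for affects how often it is found. Asking every participant at every session finds more than waiting for a call. The plan asks actively where the exposure is best protected: small supervised classes with modified poses and investigators present. It relies on calls once participants practise alone, and it names no recording step for the timed balance and floor tests.

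Two things are at stake. First, an event count from this pilot would weigh class events more heavily than events in unsupervised practice, which is the behaviour the study promotes and counts as an outcome. A larger study planned on that count could take the home setting to be quieter than it is. Second, the secondary objective concerns whether the chosen physical and psychosocial measures suit this population. A fall or new pain during a test bears on that question, and no stated step makes sure it is written down.

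**Working it through.** The plan gives no safety figure to reproduce. The check is to list every point at which the study sees or contacts participants and ask what is stated there about adverse events.

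**Inputs.** The class series is 8 weeks with two sessions a week (end of Background), the sample is 20 participants, and the physical tests are done twice.

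- Scheduled prompts in class: 8 × 2 = 16 per participant who attends every class.
- Physical test sessions: 20 × 2 = 40 at most, if everyone returns for the final tests.

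| Contact or period | Adverse-event capture stated |
|---|---|
| Baseline tests | None |
| 16 classes | Question at each session, recorded |
| Home practice during the series | Telephone instruction; can also surface at the next class |
| Practice by a participant who has dropped out | Telephone instruction only |
| Final tests | None |
| Exit interview (and dropout call) | No item on the printed form |
| Home practice after the series | Telephone instruction only |
| Three-month contact | None described; form not shown |

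**Tests.** A test visit is neither a class nor a telephone report, so the monitoring rule does not reach it. The relatedness wording does, because the tests are part of the research. The later sentence on the principal investigator's monitoring again does not, because it speaks of the yoga intervention. A test-related event is thus reportable, but no stated step detects or records it. No class follows the final tests, so the per-class question cannot pick the event up afterwards.

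**Exit interview.** The printed items cover the computer, satisfaction with classes and room, language and instructors, whether the poses work for people with arthritis, likes and dislikes, suggested changes, recommendation, and future intentions. None asks about side effects, pain, falls or injury. Where a participant rules out further classes or home practice, the example reasons offered are cost, distance, time and loss of interest. A participant could mention an injury in a free-text answer, but nobody is asked.

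**After the last class.** The described content of the three-month questionnaire is barriers and reasons for continuing or stopping. Someone who stopped because of pain may say so there. Someone who fell or had new pain, kept practising and did not telephone has no stated question that would bring it out.

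**The case against.** The strongest reply is that nothing is excluded. Participants are under a standing instruction to telephone about side effects at home, with no end date. During the series, home practice and side effects are both recorded at class, and participants keep journals. Test injuries fall within research-related events, research-related injury is evaluated, and staff associated with the study would see a fall happen. People who use walking aids, have recent or planned joint surgery, or have hyper-mobility or unstable disease are not enrolled, and all are medically cleared for light to moderate exercise. No safety endpoint is planned, and a form-level recording step is something an article may leave to the full protocol.

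Much of this stands, and it rules out three stronger readings.

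- A reader might infer that home practice lies outside adverse-event monitoring. It does not: the telephone instruction covers it.
- A reader might infer that test injuries are unreportable, or that the three-month questionnaire certainly has no adverse-event item. The relatedness wording contradicts the first. The second cannot be established, because that form is not shown.
- A reader might take three months as about 13 weeks and compute 13 / (8 + 13) = 62% of yoga exposure without active questioning. That is a share of calendar time. It is not exposure, since how many people continue, and how much, is what the study sets out to learn.

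What the reply does not remove is the imbalance. The article does more than stay silent: it states a rule, and following that rule gives active capture in class and passive capture afterwards. The missing exit item can be checked in the printed form.

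**Conclusion.** The point holds as one about ascertainment. Active questioning is stated for 16 class sessions and for no other contact described. Up to 40 test sessions have no stated capture step, and the two sentences on scope do not match. Practice after the last class, and any practice by dropouts, depends on calls that participants must start.

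The likely result is under-counting of events outside class relative to events in class. Its size cannot be given, because the article contains no event rate and no estimate of how often participants would telephone. The conclusion assumes that a direct question finds more events than a standing instruction to call, and that the undisclosed three-month form matches its description. If that form already carries an adverse-event item, the gap at three months closes, but the gaps at the tests and at exit remain.

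This is worth correcting in a pilot meant to inform a larger study. It does not show that participants are left without safety oversight.

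**What to change.** 1. Reword the monitoring sentence so that the window runs from the first study test to the three-month contact. Align the sentence on the principal investigator's monitoring with it, so that both cover testing as well as yoga.
2. Add a line to the baseline and final test forms for any fall or new pain, passed to the principal investigator through the existing route to the Medical Advisory Investigator.
3. Add one fixed question on pain, flare, fall or injury during yoga to the exit interview, including the telephone version for dropouts, and to the three-month questionnaire. Ask it of everyone, whether or not they have continued.
4. Report events by setting (class, home practice, testing) and state which were solicited and which were volunteered.

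All of this uses contacts already planned; no visit or staff member is added. The cost is a few more events to document and a possibly higher reported count, which the solicited/volunteered split lets readers interpret.

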**Figure 2 F2:**
[figure not shown]
Self care model.

The third aim is to determine the feasibility of using computerized self-interview (with assistance) to capture baseline and final health status outcomes. The previous study in this population by Wallen was completed using an in-person paper-and-pencil interview questionnaire [9,10]. In attempts to determine the feasibility for using a computerized system, this study uses a computer-assisted interview method with both the interviewer collecting baseline background information; and the respondent entering patient reported outcome measures directly into a web-based system, with assistance as needed.

Acceptability of this study will be evaluated based on the response rate, percent of classes completed, exit interview comments and the percent of patients continuing yoga after three months. Feasibility will be determined based on exit interview (see Appendix) comments and qualitative data. Qualitative field notes are kept to monitor/document related issues such as location, personnel, equipment, and the amount of modifications needed during yoga classes. Records are kept of eligible patients who decline and reasons for declining. Field notes are maintained by study investigators during recruitment, onsite yoga classes, and when interacting with study participants outside of completing questionnaires. An exit interview is completed after the last class. Those who may have dropped out of the study prior to the last class will be contacted by phone in attempts to complete the exit interview.

The feasibility of using a computerized self-interview method is based on the estimated amount of assistance needed to complete questionnaires (measured in increments from 0-100%), comments collected from the interviewer offering assistance, any technical problems encountered, and comments solicited from the participants during the exit interview.

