## Appendix: yoga study exit interview

Thank you for participating in our study. We would like to ask you some questions as you are finishing the study. Please give your honest answers to help us improve our study. Your comments are very important to us.

1. We would like to ask about your experience using the laptop computer to complete the surveys throughout the study.

a. How comfortable were you using the laptop computer? *Please circle the appropriate number below*:

Very Comfortable 1 2 3 4 5 Very Uncomfortable Comfortable

b. Do you think we should continue use computers in this way?

○ Yes

○ No

c. Is there anything else you would like us to know about your experience using the computer to complete the surveys in this study?

2. Please give us your opinion on the yoga classes and location:

a. Overall, how satisfied were you with the yoga classes? *Check one:*

○ Completely satisfied

○ Mostly satisfied

○ Equally satisfied and dissatisfied

○ Mostly dissatisfied

○ Completely dissatisfied

○ Unsure

b. How satisfied were you with the classroom where the classes were offered? *Check one:*

○ Completely satisfied

○ Mostly satisfied

○ Equally satisfied and dissatisfied

○ Mostly dissatisfied

○ Completely dissatisfied

○ Unsure

3. How much do you agree or disagree with each of the following statements? *Please circle one of the choices below.*

(SA).....Strongly agree

(A).......Agree

(N).......Neither agree nor disagree

(D).......Disagree

(SD).....Strongly Disagree

a. Yoga classes should be offered in English only

SA.….....A…......N………D….…..SD

b. Yoga classes should be offered in both English and Spanish

SA.….....A…......N………D….…..SD

c. I feel more comfortable taking yoga classes from teachers with diverse racial/ethnic backgrounds

SA.….....A…......N………D….…..SD

d. prefer taking yoga classes with others who have arthritis

SA.….....A…......N………D….…..SD

e. The yoga poses offered in class work well for people with arthritis

SA.….....A…......N………D….…..SD

4. What did you like most about the yoga classes?

5. What did you like least about the yoga classes?

6. What changes would you make in the classes to make them more helpful to your arthritis?

7. Would you recommend yoga classes to a friend with arthritis?

○ Yes

○ No

8. Now that you have completed the study, do you see yoga as a way to care for your arthritis? *Please check one of the circles below and answer the following questions*.

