○ Yes –please tell us why you see yoga as a way to care for your arthritis.

○ No – please tell us why you do not see yoga as a way to care for your arthritis.

9. How likely do you think it is that you would take another yoga class? *Check one:*

○ Extremely likely

○ Fairly likely

○ Somewhat likely

○ Slightly likely

○ Not at all*

○ Unsure

*If you answered “not at all” above, please tell us why (*for example: cost too much, too far away, don’t have time, no longer interested in yoga*).

10. How likely do you think it is that you would practice yoga on your own now? *Check one:*

○ Extremely likely

○ Fairly likely

○ Somewhat likely

○ Slightly likely

○ Not at all*

○ Unsure

*If you answered “not at all” above, please tell us why (*for example: do not have time, no longer interested in yoga*).

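### Side effects are actively asked about only in class, and the exit interview planned for dropouts has no direct question on harm or on why the person stopped, so harm-related dropout may go unrecorded

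*Protocol article*

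**What the plan says.** All of this is in the protocol article.

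- **Active enquiry.** The safety paragraphs of Methods/design (under Patient reported outcomes and psychosocial concepts) state: "Investigators will attend all yoga classes and will ask subjects about side effects during each class session". The text after Table 1 agrees: "Class attendance, the name of yoga instructor, home practice, and reported side effects are recorded during each class session".
- **Outside class.** The scope of monitoring is "Adverse events and serious adverse events will be monitored at all times during yoga classes and if reported by subjects by telephone", with the instruction "Subjects will also be instructed to report side effects immediately, to the study PI; by telephone should they occur while practicing at home".
- **Dropouts.** The text after Figure 2 says that those who "dropped out of the study prior to the last class will be contacted by phone in attempts to complete the exit interview". The analysis paragraph repeats that an exit interview will be attempted for everyone, including those who discontinue.
- **The exit interview.** The Appendix prints it item by item. Item 8 opens "Now that you have completed the study, do you see yoga as a way to care for your arthritis". Item 9 illustrates reasons for not taking another class with "for example: cost too much, too far away", followed by lack of time and lost interest. Item 10 gives only time and interest.
- **Three months.** A brief questionnaire, in person or by telephone, covers barriers and reasons for going on with or giving up yoga. It is timed from completion of the classes.

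**The concern.** Whether a participant is asked about harm depends on attendance, and harm can itself end attendance. In an arthritis population, a flare or injury that makes someone stop coming is among the events a pilot most needs to learn about. Once that person stops, the plan as written asks nothing direct about it.

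Two conclusions are exposed. The first is the safety information carried into a larger study. The second is acceptability, the primary aim: exit-interview comments and the percentage of classes completed are both named inputs to it. If the reason for stopping is not asked, a dropout caused by pain can be put down to cost, distance or lack of time.

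**Working it through.** The article gives no harm rate, harm denominator or sample-size derivation (the 20 participants are a convenience sample), so there is no figure to reproduce. The check is a comparison of the text, followed by an illustration.

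**1. Which contacts reach a participant who has stopped for good, and what do they ask?**

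- *Class enquiry:* asks about side effects directly, but no longer reaches this person.
- *Telephone report to the PI:* open to this person, but the participant must start it.
- *Exit interview by phone:* reaches this person if the call succeeds. Item 1 concerns the laptop. Item 2 is satisfaction with classes and room. Item 3 covers language, teachers, classmates and whether the poses suit people with arthritis. Items 4 to 6 ask what was liked most, liked least and should change. Item 7 asks about recommending yoga, item 8 whether yoga is a way to care for one's arthritis, and items 9 and 10 the likelihood of another class or home practice. None asks directly about side effects, worse pain, flare, injury or falls, and none asks why the person stopped. Items 9 and 10 ask for a reason only after the answer that continuing is not at all likely.
- *3-month questionnaire:* asks reasons for discontinuing, but its timing leaves coverage of dropouts unclear.
- *Outcome measures:* baseline-to-final comparisons are planned for those who complete the study, so worsening pain or function in a dropout would not appear there.

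Direct questioning on harm therefore ends when attendance ends.

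**2. Illustration of how much could be lost.** The inputs are n = 20 (from the article) and three assumptions: p, the true risk of a yoga-related harm; s, the share of harmed people who stop before being asked; and r, the chance that such a person volunteers the harm.

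Expected events on record = 20 × p × [1 − s(1 − r)]. Chance that none is recorded = {1 − p[1 − s(1 − r)]}^20.

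- p = 10%, nobody lost (s = 0, or r = 1): 20 × 0.10 = 2.0 expected; chance of none 0.90^20 = 12%.
- p = 10%, s = 0.5, r = 0.5: 20 × 0.075 = 1.5; chance of none 0.925^20 = 21%.
- p = 10%, s = 0.5, r = 0: 20 × 0.05 = 1.0; chance of none 0.95^20 = 36%.
- p = 20%, s = 0.5: 2.0, 3.0 or 4.0 events expected at r = 0, 0.5 or 1; chance of none 12%, 4% or 1%.

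**3. Why the number asked matters.** With no events among n people fully asked, the one-sided 95% upper bound is 1 − 0.05^(1/n): 13.9% for n = 20, 17.1% for 16, 19.3% for 14 and 25.9% for 10. The last case applies the 52% completion cited from the earlier randomized study (20 × 0.52 = 10.4). It is a worst case, because attrition in that study was highest before the first class.

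**The case against.** The other side has several good points.

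- **The passive route is real.** Participants are told twice to report side effects immediately. Reports are reviewed daily by the PI, and adverse events go to the Medical Advisory Investigator. Participants are also patients of the rheumatology clinic involved. A dropout who calls is recorded. This stands, but it relies on the participant's initiative.
- **Open items could bring out a harm.** Items 3e, 5, 6 and 8 all leave room for it, and field notes are kept. This also stands, but none of them asks for a harm, and nothing in the article routes such an answer to the adverse-event record.
- **The exit form measures acceptability, and the weekly flow sheet is the safety instrument.** True, but the flow sheet is described alongside class-time questioning, and a person who no longer comes to class is outside that questioning.
- **The precedent points to little loss after exposure.** In the cited study, people who started the classes mostly finished. This limits the likely size of the problem.
- **An article condenses a longer protocol.** That does not answer this point, because the interview form is printed item by item and the gap lies in its content.

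A reader might also infer that anyone who misses a class goes unasked. The documents do not support that: someone who returns is asked at the next session, so the gap concerns those who stop for good.

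**Conclusion.** The point holds in a limited form and is worth correcting. Active questioning about harm is tied to class attendance. For people who stop permanently, capture depends on a self-initiated report or a chance comment, because the contact planned for them contains no direct harm or reason-for-stopping question. Harm-related dropout may therefore go unrecorded or be read as logistics.

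The size cannot be derived from the article. The illustration rests wholly on assumed values of p, s and r. If every harmed dropout volunteers the event, or almost all attrition precedes the first class, little or nothing is lost. With 20 participants, however, one or two missed events would change the picture.

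Two stronger readings are tempting and are not supported. One is that dropouts will be counted as event-free: the article sets no harm denominator and no rule that silence means no event. The other is that the exit interview is the only contact a dropout could have: the 3-month questionnaire may reach them, although its timing suggests completers. Nor can the pilot be said to understate a harm rate by a given amount, since estimating such a rate is not among its objectives.

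**What to change.** - Add two fixed items to the exit interview, used also in the dropout call. One asks directly about new or worse pain, flare, injury, fall or other problem during classes or home practice. The other asks those who stopped why they did so, with pain, flare or injury among the options.
- Add pain, flare or injury to the example reasons in items 9 and 10.
- Give item 8 alternative wording for people who did not complete the classes.
- Send any positive answer into the existing adverse-event recording.
- State that the 3-month questionnaire also goes to dropouts.
- Report how many of the participants who attended at least one class were asked about harm.

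The cost is an amendment to a short form and a few minutes in calls that are already planned. The observed harm count may look less favourable. No treatment or clinical rule changes.
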